### Ethics

This study will be conducted in accordance with the ethical standards of the Declaration of Helsinki. This trial was approved by the institutional review board at Yeungnam University Medical Center on 12 June 2019 (IRB No. 2019–04–031-002) and registered with the clinical research information service (CRIS KCT0004063). The researcher will obtain written informed consent from the participants. The results of this study will be published in peer-reviewed medical journals.

## Discussion

The primary objective of this RCT will be to evaluate the application of NPWT to PSC after stoma reversal regarding its effectiveness in reducing the wound-healing period.

Several mechanisms contribute to the efficacy of NPWT. NPWT reduces seroma formation in a wound and stimulates angiogenesis and granulation. Negative pressure also creates a hypoxic environment in a wound, resulting in the upregulation of inflammatory cytokines, which stimulates wound healing [10, 16].

One previous RCT evaluated the application of NPWT to laparotomy wounds following abdominal surgery [10]. In this previous study, the prophylactic use of NPWT reduced the SSI rate compared to that in the control group. However, the study did not compare the wound-healing period between the two groups. Two additional studies evaluated the application of NPWT to ileostomy closure sites and demonstrated the efficacy of NPWT in reducing the SSI rate [17, 18]. However, these previous studies focused on patients with primary linear closure of stoma wounds and did not evaluate the wound-healing period.

Uchino et al. [3] conducted an RCT with a similar primary endpoint to that in the present planned trial. The authors failed to demonstrate the efficacy of NPWT in significantly reducing the wound-healing period. However, the participants of this previous RCT comprised patients with ulcerative colitis, and the opening of the PSC was wider (8 mm) than that in the present planned trial (< 5 mm). As the opening of the PSC in the present planned trial will be ≤ 0.5 cm, we believe that our trial will more likely demonstrate positive results, which may be generalised to clinical practice. Another strength of our planned trial is that we will evaluate the cost of the wound dressings, number of wound dressings, and number of hospital visits for wound dressings after discharge, as direct and indirect assessments of the convenience level and medical cost.

Although we designed this trial as a prospective RCT, several limitations exist. First, this will be a single-centre study, with a small sample size. However, we believe that the study will be adequately powered to evaluate the primary endpoint. Additionally, single-centre studies have advantages with respect to data collection consistency. Second, the assessment of the wound-healing period as a primary endpoint is subjective in nature. We plan to overcome this issue by utilising three experts to evaluate the wound directly or via photographs of the wound. However, two of the wound reviewers cannot be blinded, as one is the operator and the other is the nurse who will dress the wounds. Only one surgeon, who will evaluate the wound based on photographs, can be blinded. Third, we will enrol all types of stoma reversal surgeries, regardless of the patient’s stoma type (e.g. loop ileostomy, loop colostomy, end colostomy, etc.). This may lead to a large bias in the study; however, we believe that the inclusion of all stoma types will benefit the generalisability of the results. The stoma reversal technique will be performed in the same manner regardless of the stoma type, and the endpoints of the SR-PICO study will be limited to the evaluation of the wound at the stoma reversal site.

In conclusion, the SR-PICO trial is a planned RCT to evaluate the efficacy of NPWT in reducing the wound-healing period in patients who undergo stoma closure using the PSC method. We believe that the results of the SR-PICO trial will clarify the role of NPWT in patients undergoing stoma reversal and strengthen the rationale for choosing a dressing technique.

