### Interventions

All participants will be randomised to either the intervention group or the control group, using a 1:1 ratio. The randomisation allocation will be generated using a computerised randomisation system and applied immediately after fascia occlusion to avoid a performance bias.

Stoma reversal will be performed using standard techniques, with the patient under either spinal or general endotracheal anaesthesia, and the bowel anastomosis will be either stapled or hand sewn at the discretion of the surgeon. After fascia closure, skin closure will be performed with the PSC method using absorbable monofilament suture material (2–0 Monocryl; Ethicon, Cincinnati, OH, USA), leaving an opening ≤ 0.5 cm (approximately). Subsequently, a simple, transparent, waterproof dressing will be applied to patients in the control group, and a PICO™ portable NPWT device (Smith & Nephew Healthcare, Hull, UK) dressing will be applied to patients in the intervention group (Fig. 3).

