### Sample size calculation

The target sample size will be 38 participants, as this will provide 80% power at the 5% (two-sided) level of significance to detect a 7-day reduction in the wound-healing period in the intervention group compared to that in the control group (superiority design, 19 ± 7 days vs 26 ± 7 days), with allowance for 10% attrition. The anticipated wound-healing period in the control group is based on data from a previous RCT that compared the healing times of the stoma reversal site between conventional linear closure and PSC [6]. We expect to screen approximately 44 patients for eligibility during the study period (*n* = 22 per year), based on the mean number of stoma reversal cases at our institution in the last 2 years. The length of the study period was decided with consideration of the expected screening number and a dropout rate of 20% (due to exclusion and refusal to consent).

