### Statistical analysis

No interim analyses will be conducted due to the small sample size of the study. All analyses of the primary/secondary endpoints will be conducted with the intention-to-treat population. A per-protocol analysis will be also performed for further comparisons. Normally distributed data will be examined using Student’s *t* test. Non-normally distributed data will be examined using the Mann–Whitney *U* test. The chi-square or Fisher’s exact test will be used to examine categorical variables. *p* < 0.05 will be considered statistically significant.

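### The plan names stoma type as a possible source of large bias, but every test it states ignores stoma type; a prespecified adjusted primary comparison would handle chance imbalance at little cost

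*Protocol article*

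**What the plan says.** The limitations paragraph of the Discussion states "we will enrol all types of stoma reversal surgeries" and gives loop ileostomy, loop colostomy and end colostomy as examples. It then says "This may lead to a large bias in the study". It offers three points in reply: wider generalisability, a reversal technique that does not vary with stoma type, and endpoints confined to the wound at the reversal site.

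The Statistical analysis section fixes the tests for the primary and secondary endpoints in the intention-to-treat population, with a per-protocol analysis alongside. The sentence that begins "Normally distributed data will be examined using" names Student's t test. Non-normal data go to the Mann–Whitney U test, and categorical data to chi-square or Fisher's exact. No covariate or stratum is mentioned.

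The Interventions section says "All participants will be randomised to either the intervention group or the control group, using a 1:1 ratio" and that a computerised system generates the allocation. It does not say whether any factor is stratified.

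The Sample size calculation section gives "The target sample size will be 38 participants", for "80% power at the 5% (two-sided) level of significance", on "superiority design, 19 ± 7 days vs 26 ± 7 days", "with allowance for 10% attrition".

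**The concern.** The article identifies one baseline factor that might distort the result and then states an analysis that cannot use it. The test is stated outright, so this is not a detail left to an unseen analysis plan. None of the three replies in the Discussion deals with an imbalance that arises by chance. Generalisability is a separate matter. A uniform technique and wound-only endpoints may reduce how much stoma type matters, but they do nothing about whatever difference remains.

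In a trial of 38 patients, a chance gap between arms on a prognostic factor can move the estimate by a noticeable part of the 7-day target. A reader who then sees an uneven baseline table cannot tell how much of the observed difference is due to treatment. An adjusted analysis added after the imbalance is seen would be open to the charge of selection; one fixed beforehand would not. If stoma type does predict healing time, adjustment would also reduce the residual variance in a design with little spare power.

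**Working it through.** **Inputs from the protocol article.** Difference 7 days (26 − 19), SD 7 days, two-sided 5%, 80% power, 10% attrition, 38 patients (Sample size calculation section).

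**Inputs assumed, because the documents do not give them.** Share of colostomies p = 30%, so 10 of 34 evaluable patients. Difference in mean healing time between ileostomy and colostomy sites D = 0, 3, 5 or 7 days. The total within-arm SD stays at 7 days.

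**1. The plan's own figure.** The two-sample t test at a standardised difference of 7/7 = 1 needs 16.71, so 17 per arm and 34 in total. Then 34/0.90 = 37.8, rounded up to 38. The stated number reproduces. Unadjusted power at 17 per arm is 80.7%, and the standard error of the difference is 7 × √(2/17) = 2.40 days.

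**2. Chance of imbalance.** With 10 colostomies among 34 patients split 17 and 17, the number in one arm is hypergeometric(34, 10, 17). A gap of at least 4 means a split of 7–3 or more extreme:

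- 2 × (0.1009 + 0.0252 + 0.0032 + 0.0001) = 0.259.
- A gap of at least 6 has probability 0.057.

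The result depends on the mix. The probability of a gap of at least 4 is 0.085 with 7 colostomies (20%) and 0.169 with 17 (50%). All of these take allocation that is not stratified by stoma type.

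**3. Shift in the unadjusted estimate.** The shift is (gap/17) × D. For a gap of 4:

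- D = 5: 4/17 × 5 = 1.18 days.
- D = 7: 4/17 × 7 = 1.65 days.

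These are 0.5 and 0.7 of the standard error (1.18/2.40 and 1.65/2.40).

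**4. Power with adjustment.** Variance explained is R² = p(1 − p)D²/49. The residual SD is 7√(1 − R²). The standard error is that SD × √(2/17) × √(1 + 1/31), where the last factor is the average price of chance covariate imbalance. Power comes from the noncentral t on 34 − 3 = 31 degrees of freedom.

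| D (days) | R² | Residual SD | SE (days) | Adjusted power | Unadjusted power |
|---|---|---|---|---|---|
| 0 | 0 | 7.00 | 2.44 | 79.4% | 80.7% |
| 3 | 0.039 | 6.86 | 2.39 | 80.9% | 80.7% |
| 5 | 0.107 | 6.61 | 2.31 | 83.7% | 80.7% |
| 7 | 0.210 | 6.22 | 2.17 | 87.8% | 80.7% |

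**5. Type I error.** This was simulated with 20,000 trials per setting, 17 per arm, each patient a colostomy with probability 0.3, and no treatment effect. Over all trials the t test rejects in about 5%. Among the roughly 19% of trials whose arms differ by at least 20 percentage points in stoma type, it rejects in 7.5% (D = 5) and 11.3% (D = 7). The adjusted analysis rejects in 5.1% and 5.8% of those same trials.

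**The case against.** The strongest reply is that nothing here is invalid. Randomisation makes the arms comparable in expectation, the unadjusted test holds 5% over all trials, and the sample size matches that test exactly. The word bias in the Discussion is then loose wording in a limitations paragraph. All of this stands. A reader might infer from the article's own words that the comparison will be biased, but the design does not support that.

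Next, the effect of stoma type is conjecture. The article says only that it may matter, and the closure method, suture material and approximate opening size are the same for everyone, which could make stoma type nearly irrelevant to healing of that opening. This stands as a limit on size. Differences of 5 to 7 days are large beside a 7-day target. At 3 days adjustment gains essentially nothing, and at 0 it costs about 1 point of power. It does not remove the point, because the article itself raises the factor and the possible loss is small.

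A reader might also infer that the allocation is unstratified and ask for it to be changed. The documents do not support that. The Interventions section is silent on stratification, a journal article commonly leaves this to the full protocol, and enrolment had already begun. If the full protocol does stratify by stoma type, the imbalance figures above fall away, and the analysis would have further reason to use the factor.

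**Conclusion.** The point holds as a mismatch between a factor that the article flags and a stated analysis that ignores it. It is not an error in the sample size or in the validity of the test. What is at stake is the correction of a chance imbalance, and possibly some precision.

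Under the assumed 30% colostomy share, a gap of at least 4 patients arises in about one trial in four, which is neither rare nor likely. It moves the estimate by 1.2 to 1.6 days if the types differ by 5 to 7 days. The change in power from adjusting runs from about −1 point (no stoma-type effect) through nil (3 days) and +3 (5 days) to +7 (7 days). It would be too strong to say that precision is certainly being lost: that needs a sizeable stoma-type effect, which the documents do not establish. The case for acting is that at most about 1 point is at risk, and that the remedy counts as prespecified only if it is written down in advance.

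**What to change.** Before any outcome data are compared, state that the primary comparison is adjusted for stoma type in two levels, ileostomy versus colostomy. Use a linear model with treatment and stoma type. If the data are judged non-normal, use a rank test stratified by stoma type (van Elteren) in place of the plain Mann–Whitney test. Keep the unadjusted test now stated as a sensitivity analysis.

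The cost is a few lines of text, one degree of freedom, and about 1 point of power if stoma type does not predict healing. Two levels avoid sparse strata but merge loop and end colostomies. The documents give no basis for a finer split, so the grouping should be fixed in the same text. Stoma type is known before surgery, so no new data are needed. The timing allows the change: the Trial status section reports seven patients enrolled by 22 October 2019, and no interim analysis is planned.

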### Trial status

This trial (protocol version 1.1) is in the ongoing recruitment phase, which started on 25 June 2019. The first participant was enrolled on 14 July 2019 and seven participants have been enrolled in the study as of 22 October 2019. The study will be completed on 30 June 2021.

## Data Availability

The data collected in the SR-PICO study will be publicly available online upon trial completion.

## Abbreviations

CRIS: Clinical Research Information Service
NPWT: Negative-pressure wound therapy
POSAS: Patient and observer scar assessment scale
PSC: Purse-string closure
RCT: Randomised controlled trial
SSI: Surgical site infection
